## Abstract

**Background:**

This study aims to investigate the effects of a modified, balanced crystalloid including phosphate in a perioperative setting in order to maintain a stable electrolyte and acid-base homeostasis in the patient.

**Methods/design:**

This is a single-centre, open-label, randomized controlled trial involving two parallel groups of female patients comparing a perioperative infusion regime with sodium glycerophosphate and Jonosteril® (treatment group) or Jonosteril® (comparator) alone. The primary endpoint is to maintain a stable concentration of weak acids [A^-^] according to the Stewart approach of acid-base balance. Secondary endpoints are measurement of serum phosphate levels, other acid-base parameters such as the strong ion difference (SID), the onset and severity of postoperative nausea and vomiting (PONV), electrolyte levels and their excretion in the urine, monitoring of renal function and glycocalyx components, haemodynamics, amounts of catecholamines and other vasopressors used and the safety of the infusion regime.

**Discussion:**

Perioperative fluid replacement with the use of currently available crystalloid preparations still fail to maintain a stable acid-base balance and experts agree that common balanced solutions are still not ideal. This study aims to investigate the effectivity and safety of a new crystalloid solution by adding sodium glycerophosphate to a standardized crystalloid preparation in order to maintain a balanced perioperative acid-base homeostasis.

**Trial registration:**

EudraCT number 201002422520. Registered on 30 November 2010.

**Electronic supplementary material:**

The online version of this article (doi:10.1186/s13063-017-2051-z) contains supplementary material, which is available to authorized users.

## Background

The increasing importance of an adequately balanced crystalloid in terms of outcome has been shown by a range of review articles [1–4]. Current studies target to find the “ideal physiologic” crystalloid preparation, resembling plasma concentrations, maintaining electrolyte concentrations within normal range and stabilizing acid-base balance. In the beginning of the 1990s it was shown that the (excessive) administration of isotonic saline resulted in an acid-base dysbalance, a hyperchloraemic acidosis [5] that can effectively mask perfusion deficits or result in inadequate therapeutic interventions if this condition is mistaken as tissue hypoxia [6]. Furthermore, we now know that a perioperative hyperchloraemic acidosis induced by administration of saline results in a reduction of renal perfusion and/or urinary excretion [7] as well as in a higher incidence of postoperative nausea and vomiting (PONV) morbidity and mortality [3, 4, 8–11]. Imbalances in acid-base chemistry can be described with the help of (1) the descriptive Henderson-Hasselbalch equation [12], where the blood pH is related to the bicarbonate buffer system, (2) a semiquantitative method using the later introduced concepts of base excess (BE) [13] and anion gap (AG) [14] as computable factors and (3) the quantitative physicochemical approach by Peter Stewart, which has been intensively discussed in the 1990s but now has been mostly accepted to be the “gold standard” [15–17]. The advantage of Stewart’s concept is its quantitative analytical approach that permits one to diagnose and differentiate between specific forms of acid-base disturbances that conventional methods have not been able to describe before [18].

Stewart based his model on three principles: (1) the sum of all positive charges equals the sum of all negative charges (principle of electroneutrality), (2) the dissociation equilibria of all incompletely dissociated substances must always be satisfied and (3) the total mass of a non-completely dissociated substance can be calculated by summarizing the amount of dissociated and non-dissociated forms. Three components comply to these principles at all times: (1) H_2_O in its dissociated form [H^+^] and [OH^−^] (however, the plasma concentration of these ions is extremely low (approximately 10–7 mmol/l)), (2) strong ions, such as electrolytes ([Na^+^], [K^+^], [Cl^−^], [Ca^2+^], [Mg^2+^] and lactate, which are found nearly completely dissociated and can, therefore, hardly react with other substances in the human body, and (3) weak (= incompletely dissociated) substances comprised of acid-base pairs (carbonic acid/carbon dioxide, NH_3_/NH_4_
^+^) as well as non-volatile plasma proteins and phosphate [16, 18]. Stewart rigorously distinguished between three *dependent variables* the pH and the concentration of hydrogen ions [H^+^] and bicarbonate [Bic^−^] that can only passively respond to alterations determined entirely by three *independent variables*, the carbon dioxide partial pressure (paCO_2_), the weak acids [A^−^] (former [A_TOT_]) and the strong ion difference (SID, see below). Stewart also employed the Henderson-Hasselbalch equation to relate respiratory acidosis/alkalosis to changes of the paCO_2_; however, according to his model, a metabolic acidosis/alkalosis cannot be explained with it [16, 18]. Contemplating the other two independent variables, Stewart proposed that electrolytes, as well as albumin and phosphate, can shift the pH; an entirely new perspective. Currently, there are a couple of formulas proposed to calculate the SID. For the present study we will use the following formulas for [A^−^] and the SID published by Figge et al. [19]:1$$ \mathrm{S}\mathrm{I}\mathrm{D}=\left[{\mathrm{Na}}^{+}\right]+\left[{\mathrm{K}}^{+}\right]-\left(\left[{\mathrm{Cl}}^{-}\right]+\left[{\mathrm{Lac}}^{-}\right]\right) $$
2$$ \left[{\mathrm{A}}^{-}\right]=\left[\mathrm{Alb}\times \left(0.123\times \mathrm{pH}-0.631\right)\right]+\left[\mathrm{Pix}\left(0.309\times \mathrm{pH}-0.469\right)\right] $$

where [Na^+^] = sodium, [K^+^] = potassium, [Cl^−^] = chloride, [Lac^−^] = lactate, [Alb] = albumin in g/L and

[Pi] = phosphate in mmol/l concentrations in the serum.

Normal values for the SID and [A^−^] in human plasma at a pH of 7.4 lie around 40 meq/l and 15 meq/l, respectively. The unit milliequivalents per litre (meq/l) refers to the electric charge (e.g., 2 mmol [Na^+^] = 2 meq). Therefore, a normal SID can be calculated with formula (1) as follows:

SID = (142 meq/l) + (4 meq/l) – (105 meq/l) – (1 meq/l) = 40 meq/l.

The following relationship between SID, [A^−^] and the pH has been established:$$ \mathrm{S}\mathrm{I}\mathrm{D}\uparrow \mathrm{and}/\mathrm{or}\left[{\mathrm{A}}^{-}\right]\downarrow \kern2.75em \to \kern2.5em \mathrm{Alkalosis} $$
$$ \mathrm{S}\mathrm{I}\mathrm{D}\downarrow \mathrm{and}/\mathrm{or}\left[{\mathrm{A}}^{-}\right]\uparrow \kern2.75em \to \kern2.5em \mathrm{Acidosis} $$

Applying this concept, it becomes evident that an increase in chloride lowers the SID, leading to the previously mentioned hyperchloraemic acidosis and that hypoalbuminemia lowers [A^−^], shifting the balance towards an alkalotic state. These new insights into the cause of different types of metabolic acid-base disorders comprise the novelty and ingenuity of Stewart’s concept.

### Trial rationale and hypothesis

Many crystalloid preparations contain a non-physiologic concentration of electrolytes. Although the unprotected term “balanced” is widely used for different crystalloid preparations by authors and manufacturers, there is currently no perfectly balanced preparation available. NaCl 0.9% w/v (isotonic saline) solution consists of 154 mmol/l (=154 meq/l) [Na^+^] and 154 mmol/l (= 154 meq/l) [Cl^−^]. The SID of 0.9% isotonic saline is, therefore, 0 meq/l. The administration of large amounts of saline will dilute the patient’s former physiologic SID resulting in acidosis. Ringer’s lactate and other balanced solutions show a SID of 27 − 36 meq/l which is much closer to physiologic values [20, 21]. This was acquired by replacing a certain amount of chloride with a metabolizable anion like lactate, acetate or maleate. Though better balanced than 0.9% isotonic saline, these solutions neither contain albumin nor phosphate and, thus, cannot prevent the dilution of [A^−^] and hence the possible onset of an alkalotic state if infused in humans. As a consequence, they are not really “balanced” in the sense of Stewart’s approach. The key aspect of the planned investigation is to test the applicability of a new phosphate-balanced crystalloid preparation based on Stewart’s concept of acid-base. The novelty of this study is the fact that sodium glycerophosphate is administered in patients undergoing major abdominal surgery not to replenish low phosphate levels as a therapeutic approach, but to stabilize them pre-emptively.

We hypothesize that the patients’ [A^−^] levels can be stabilized when adding phosphate to a standard crystalloid. Additionally, in contrast to the control group, perioperative hypophosphatemia can be avoided by the supplementation of phosphate. It will, therefore, be tested whether Jonosteril® (Fresenius Kabi AG, Bad Homburg, Germany, see below) (investigational medical product 1 (IMP1)) in combination with sodium glycerophosphate (Fresenius Kabi AG, Bad Homburg, Germany) (IMP2)) is able to maintain a more constant acid-base balance in the patient compared to Jonosteril® alone. Additionally, a reduction of PONV is possible. Both preparations are approved substances and frequently administered during daily clinical routine.

### Jonosteril®

The crystalloid Jonosteril® is routinely administered for perioperative fluid therapy at the authors’ institution. It contains electrolytes in physiologic concentrations as well as acetate (Na^+^ 137 mmol/l, K^+^ 4 mmol/l, Ca^2+^ 1.65 mmol/l, Mg^2+^ 1.25 mmol/l, Cl^−^ 110 mmol/l, acetate^−^ 36.8 mmol/l); however, it does not carry albumin or phosphate. As such, this crystalloid is capable to maintain a SID within normal range; it will, however, not be able to prevent a decrease of [A^−^] due to the occurring dilution [22]. The latter and the decrease of albumin and phosphate will most likely result in hypoalbuminemia, shifting the system towards alkalosis. Contraindications for the use of Jonosteril® are any form of hypersensitivity or allergy to the components of the crystalloid as well as hyperhidratation and hyperkalaemia, according to the manufacturer. Only the crystalloid Jonosteril® will be tested in this study, further studies will be necessary to evaluate the applicability also for other crystalloid preparations.

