### Sodium glycerophosphate

Sodium glycerophosphate (Fresenius Kabi AG, Bad Homburg, Germany; concentration 1 mmol/ml, ATC-Code: B05XA) is an electrolyte supplement approved and routinely administered for the parenteral treatment of hypophosphatemia especially on intensive care units (ICUs). Phosphate is usually not routinely measured during surgical procedures and is, therefore, not substituted. Accordingly, a hypophosphatemia occurs frequently with an incidence of between 44.8% [23] and 67% [24] and remains undetected, although the unfavourable effects in terms of post-aggression metabolism are well known. The ATP- dependent metabolism strongly relies on phosphate as a substrate, especially during the postoperative phase of major cardiac and abdominal surgery [25, 26]. This leads to a high turnover of phosphate and requires parenteral substitution. Therefore, an intraoperative substitution of phosphate seems reasonable and indicated. It has been shown that an early perioperative substitution of phosphate during liver surgery had a protective effect in terms of cardiorespiratory complication and is, therefore, recommended [27, 28]. Prior to inclusion, all patients will be evaluated regarding contraindications for the use of sodium glycerophosphate (existing chronic kidney disease or renal failure, hyperphosphatemia, hypernatremia or allergic disposition towards sodium glycerophosphate or its components). If none of the above can be detected, the parenteral application of sodium glycerophosphate is uncritical. By contrast to the dosage given on ICUs [29] or according to an estimated basic daily demand of 0.2–0.5 mmol/kg bodyweight (according to the summary of product characteristics) the amount of phosphate given during this trial is low. The maximum infusion rate is 20 mmol phosphate per hour according to the manufacturer and will not be reached. It is expected that during the observation period and due to the substitution, serum phosphate levels will rise around 0.5 mmol/l [22] which will be controlled every 30 min. Since the substituted phosphate gets rapidly metabolized and excess phosphate is excreted in the urine, a severe hyperphosphatemia is not expected [30]. Before initiation of the trial, it was confirmed that Jonosteril® and sodium glycerophosphate are compatible for the intended use. Phosphate will be added to Jonosteril® immediately prior to the application to avoid any potential risk of infection.

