### Secondary objectives

The secondary objectives of the trial are the influence of the distinct infusion therapy regimens on other acid-base parameters, on the onset of PONV, laboratory chemical parameters like electrolytes and their excretion in the urine, as well as hemodynamic stability, monitoring of the vascular barrier (shedding of the glycocalyx), the the use of vasopressors and the safety of the crystalloid preparation in this setting.

Secondary endpoints of the trial are:Serum phosphate levels (ionized in mmol/l, non-ionized in mg/dl, continuous measure from baseline T0 and serial blood draws over a 120-min time frame T1 − T5)Acid-base parameters: pH (numerical), paCO_2_ (mmHg), HCO_3_
^−^ (mmol/l), BE (mmol/l), anion gap (mmol/l); (continuous measure from baseline T0 and serial blood draws over a 120-min time frame T1 − T5)Apparent SID and effective SID (both in mmol/l), Strong Ion Gap (mmol/l), albumin, lactate (ionized in mmol/l, non-ionized in mg/dl, continuous measure from baseline measures T0 and serial blood draws over a 120-min time frame T1 − T5) serum and urine analysis of electrolytes (osmolality in mosmol/l; all other in mmol/l, continuous measure on T6, change from baseline T0)Documentation and analysis of mean arterial blood pressure (MAP) in mmHg, heart frequency in min^-1^, demand of vasopressors (norepinephrine dose in mg/h), stroke volume variation (SVV) in %, central venous pressure (CVP) in mmHg and cardiac output in ml/min (continuous measure from baseline T0 and serial blood draws over a 120-min time frame T1–T5)Assessment of serum creatinine (mg/dl) and urea (mg/dl) as well as calculation of the glomerular filtration rate (ml/min) and creatinine clearance (C_cr_) in ml/min according to the Cockroft-Gault equation [31] as continuous measure on two blood draws at T0 and T6, change from baseline T0)
$$ {\mathrm{C}}_{\mathrm{cr}}=\frac{\left(140-\mathrm{Age}\ \mathrm{in}\ \mathrm{years}\right) \times \mathrm{Mass}\ \left(\mathrm{in}\ \mathrm{kg}\right) \times \left[0.85\ \mathrm{if}\ \mathrm{female}\right]}{72 \times \mathrm{Serum}\ \mathrm{Creatinine}\ \left(\mathrm{in}\ \mathrm{mg}/ dl\right)} $$

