### Pilot phase

The first six patients will receive Jonosteril® together with sodium glycerophosphate (IMP1/IMP2 protocol) in concentrations ranging from 1 to 6 mmol/l (Na^+^: 139–149 mmol/l) to evaluate the most suitable concentration for the following randomization phase. We will test a concentration of 4 mmol/l phosphate (= 2 ml sodium glycerophosphate per 500 ml Jonosteril®) initially. This solution will contain 145 mmol/l sodium. Repeated measurements of serum phosphate levels will shed light on the efficacy of the measure. In the case that serum phosphate levels do not remain stable within the normal range, we will gradually adapt the dose until stable levels are achieved. Patients will not receive a concentration higher than 6 mmol/l since then the sodium levels would surpass the maximum threshold value.

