### Randomization phase

After the pilot phase, in which the most suitable phosphate concentration is determined, a total of 42 patients, 21 per group, will be allocated to one of the two study arms by randomization:Jonosteril® and sodium glycerophosphate (IMP1/IMP2) (treatment group)Jonosteril® (IMP1) (control group)

All patients will receive the study medication according to their allocation over 120 min after the initiation of general anaesthesia in a maximum dose of 30 ml per ideal bodyweight (IBW = height (in cm) − 100) per hour for losses due to insensible perspiration, urinary output and extracellular deficits due to the fasting state as well as five times the estimated blood loss [32, 33]. The rationale for the use of the amount of fluids is based on previous studies and the demand-oriented current clinical practice. This is in concordance with previous studies using similar regimes. The recruited patients have a higher fluid demand [32, 33]. Hofmann-Kiefer et al. showed that a maximum of 30 ml/kg/bodyweight was necessary to keep patients hemodynamically stable and distinct acid-base alterations were described. Over the time course of 120 min, the patients likely suffer from a blood loss of 1000 ml or more. According to current clinical practice, a blood loss should be replaced in a ratio of 4–5:1 with crystalloids [33]. Taken together, our approach using 30 ml/kg/ideal bodyweight seems reasonable for this patient cohort. Measurements will take place every 30 min: baseline (T1), 30 min (T2), 60 min (T3), 90 min (T4) and 120 min (T5) and parameters will be documented by the investigators in the Case Report Forms (CRF) of each participant. An overview of the parameters assessed in this study and their respective time points is provided in Table 1.

**Table 1 Tab1:** Parameters measured at the distinct time points

Measurement	Time point
Haemodynamic values	
Norepinephrine dose (mg/h)	T1–T5
Heart rate (min^-1^)	T1–T5
Systolic blood pressure (mmHg)	T1–T5
Diastolic blood pressure (mmHg)	T1–T5
Central venous pressure (mmHg)	T1–T5
Stroke volume variation (%)	T1–T5
Cardiac output (ml/min)	T1–T5
Blood loss (ml)	T1–T5
Haemoglobin (g/dl)	T1–T5
Haematocrit (%)	T1–T5
Urine volume (ml)	T1–T5
Crystalloid administered (ml)	T1–T5
Serum electrolytes	
[PO_4_ ^3-^] ionized (mmol/l)	T0–T5
[PO_4_ ^3-^] (mg/dl)	T0–T5
[Na^+^] (mmol/l)	T1–T5
[K^+^] (mmol/l)	T1–T5
[Cl^−^] (mmol/l)	T1–T5
[Mg^2+^] (mmol/l)	T1–T5
[Ca^2+^] (mmol/l)	T1–T5
Osmolality (mosmol/l)	T1–T5

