#### Exclusion criteria

Subjects showing the following exclusion criteria cannot be included in the trial:Participation in another clinical trialPatients who are not personally able to give their informed consentPatients at a childbearing age without using contraceptivesAcute or chronic renal failure (glomerular filtration rate <60 ml/min)Patients suffering from an acid-base-disturbance (i.e. severe acidosis)Patients suffering from acid-base disturbances caused by SIRS or sepsisPregnancy or lactation period (pregnancy testing will be executed at least 1 day prior to the surgical procedure)Oedema, hypertonic dehydratation, hyperhidratationHyperphosphata emia, hypernatraemia, hypocalcaemia (according to the standard normal laboratory values of the authors’ institution)A known hypersensitivity against the test drugs and/or their componentsA known history or active abuse of alcohol and/or drugs

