#### Sample size calculation

We calculated the sample size using the statistic software SAS (SAS Institute GmbH, Heidelberg, Germany). This study has an explorative character and is supposed to deliver first-ever data. There is currently no comparative data available for the medication group or time intervals considered. For the control group regimen, there is data available from a previous study [22] for two time points (60 min and 120 min after exposure). Therefore, we considered the deviation of [A^−^] at the time point T5 (120 min) compared to baseline T1 (0 min) applying a *t* test. We expect normally distributed data since the control group data derived from the previous study showed the same characteristics [22]. We set the level of significance to 5% and the power to 80% resulting in 21 patients per group. With the addition of swix patients for the pilot phase, the total number of patients is 48.

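### Hyperkalaemia is a stated contraindication to Jonosteril, which every participant receives, but it is not an exclusion criterion

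*Protocol article*

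**What the plan says.** The Jonosteril section of the protocol article gives the contraindications to the fluid as hypersensitivity or allergy to its components, "as well as hyperhidratation and hyperkalaemia, according to the manufacturer".

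The Exclusion criteria rule out hypersensitivity to the test drugs and rule out hyperhydration. A separate electrolyte item lists hyperphosphataemia together with "hypernatraemia, hypocalcaemia (according to the standard normal laboratory values" of the institution). Potassium does not appear there, nor in the Inclusion criteria.

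The Sodium glycerophosphate section says that, before inclusion, "all patients will be evaluated regarding contraindications for the use of sodium glycerophosphate". No such check is described for Jonosteril.

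Every participant is given Jonosteril. In the Pilot phase section, "The first six patients will receive Jonosteril® together with sodium glycerophosphate". In the Randomization phase section, one arm receives it with sodium glycerophosphate and the other receives it alone.

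**The concern.** Eligibility criteria should keep out patients for whom the protocol says an investigational product is contraindicated. Jonosteril is one of the two investigational products here (IMP1), and it is infused in volume: up to 30 ml per kg ideal bodyweight per hour for 120 min. If one of its contraindications has no matching exclusion, and nothing else in the document does that work, site staff who follow the printed list correctly could still enrol a contraindicated patient. This is a question of participant safety and of consistency within the document. It does not bear on the validity of the comparison.

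**Working it through.** **Step 1: match each stated contraindication to an exclusion.**

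| Product | Contraindication stated in the article | Counterpart in the Exclusion criteria |
|---|---|---|
| Jonosteril | Hypersensitivity or allergy | Yes (test drugs or components) |
| Jonosteril | Hyperhydration | Yes |
| Jonosteril | Hyperkalaemia | **None** |
| Sodium glycerophosphate | Chronic kidney disease or renal failure | Yes (renal failure, GFR below 60 ml/min) |
| Sodium glycerophosphate | Hyperphosphataemia | Yes |
| Sodium glycerophosphate | Hypernatraemia | Yes |
| Sodium glycerophosphate | Allergy | Yes (test drugs or components) |

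Jonosteril has 2 of 3 matched and sodium glycerophosphate 4 of 4. Hyperkalaemia is the only one of the seven without a counterpart. The list does exclude hypocalcaemia, which the article names as a contraindication to neither product. No reason is given for leaving potassium out, so this reads as an oversight.

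**Step 2: look for another provision that closes the gap.**

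- *Inclusion criteria:* sex, ASA class, type of surgery, planned catheters, consent and age. There is no laboratory limit.
- *Pre-inclusion contraindication check:* stated for sodium glycerophosphate only, and its list has no potassium item.
- *Renal and acid-base exclusions:* these remove some patients likely to be hyperkalaemic, but neither is a potassium criterion. Raised potassium with GFR of 60 ml/min or more and no acid-base disturbance is not excluded.
- *Potassium measurements:* Table 1 lists serum potassium at T1–T5, and T1 is 0 min, after enrolment. The Secondary objectives section does mention a T0 baseline for electrolytes ("continuous measure on T6, change from baseline T0"), but as part of an endpoint. Nothing links a T0 or T1 potassium value to eligibility or to withholding the infusion.

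None of these closes the gap.

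**Step 3: count who receives the fluid.**

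6 pilot + 2 × 21 randomized = 6 + 42 = 48. This agrees with the Sample size calculation section: "the total number of patients is 48". All 48 receive Jonosteril. That is the number exposed to the product, not the number at risk; the article gives no frequency of hyperkalaemia.

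**Step 4: put the potassium content in scale.**

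The article gives no body weights, so ideal bodyweight is assumed to be 50 to 80 kg (heights of 150 to 180 cm by the protocol's formula). At the maximum dose over 2 h:

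- volume = 30 ml/kg/h × 2 h × 50 kg = 3.0 l, up to 30 × 2 × 80 = 4.8 l;
- potassium = 4 mmol/l × 3.0 l = 12 mmol, up to 4 × 4.8 = 19.2 mmol.

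The concentration of 4 mmol/l equals the normal serum potassium in the article's worked strong ion difference example. These figures therefore do not show that the infusion would raise serum potassium, and that is not claimed.

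**The case against.** The strongest reply is that this is an omission rather than a contradiction. No sentence says that hyperkalaemic patients may be enrolled, and a labelled contraindication to an approved, routinely used fluid does not lapse because an exclusion list fails to repeat it. An anaesthesiologist investigator is present throughout the observation period, potassium is measured at 0 min and every 30 min, and the renal and acid-base exclusions already remove some of the likeliest cases. The article also condenses a fuller protocol that is not shown.

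Much of this stands as an argument about weight. The safeguards are real, no harm can be quantified, and the lack of a described pre-inclusion check for Jonosteril could be a product of condensation, so little should rest on that alone.

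It does not remove the mismatch. The exclusion list is printed item by item and names three other electrolyte disorders, so two statements in the same document can be compared directly. Clinical vigilance would equally catch hypernatraemia or hypocalcaemia, yet both are listed. Monitoring from 0 min onward comes after enrolment and is not an eligibility rule.

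**Conclusion.** The point holds. The eligibility criteria do not carry over one of the three contraindications that the protocol itself states for the fluid given to all 48 patients, and no other provision supplies it.

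Its size is small. Few elective patients are likely to be hyperkalaemic (a judgement, since the article gives no figure), the fluid's potassium concentration is physiological, and potassium is followed closely during the infusion. The primary endpoint, sample size and analysis do not change. The conclusion rests only on the printed criteria being those used at screening. It is worth correcting because it concerns participant safety and the remedy is simple.

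**What to change.** Add hyperkalaemia to the electrolyte item of the Exclusion criteria, defined as for the other electrolytes by the institution's normal laboratory values. State that it is judged on a pre-operative potassium value available before enrolment. If the sponsor considers the contraindication immaterial for a fluid with 4 mmol/l potassium, the protocol should say so and give the reason.

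The cost is one added item and a pre-operative potassium result. Sodium, calcium and phosphate already have to be known to apply the existing exclusions. At most a few patients would be screened out, before randomization, so the target of 21 per group is untouched. The Trial status section reports that recruitment is under way, so the change would protect later enrolees, and it can go to the authorities by the route for modifications that the Ethics and Good Clinical Practice section describes.
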